### 1.3. Secondary Goals

To understand the effect of both the dosage of hospital treatment and home treatment by parents (economic analysis/resource efficiency).To study the natural history of the rate of development of gross motor function in children under one and a half years of age with neuromotor alterations (pre-rehabilitation intervention).To assess the long-term impact on the gross motor function of children with neuromotor disorders undergoing Vojta therapy compared to children treated without this methodology.

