## 2. Materials and Methods

### 2.1. Study Design

A pseudo-randomized clinical trial has been designed that will assess gross motor function before the physiotherapy intervention (with Vojta therapy or conventional physiotherapy intervention, such as environmental enrichment and task-specific training) and two months after its application. The clinical trial has been conducted according to the consolidated standards of reporting trials (CONSORT) statement [40]. The current treatment protocol is described according to the recommendations of SPIRIT [41].

Patients are assigned to one treatment or another following criteria of immediacy as part of the regular routine of the rehabilitation service. Therefore, the randomization of the sample is possible following the natural ordering of the rehabilitation service where the study is carried out. The participants in this research, within their care routine and according to the health protocols established in the service, will be assigned to one of the two study groups:Intervention group: patients under Vojta Therapy intervention [17,18,19,20,21,22,23,24,25,26,27,28]Control group: patients under regular physiotherapy intervention, such as environmental enrichment and task-specific training [25]

This methodology will be useful to provide a service evaluation of the operation of the rehabilitation service itself.

Neither the therapists nor the evaluators of the GMFM may be blinded to the type of treatment administered due to the organization of the rehabilitation service where the study is carried out, as well as the “face-to-face” requirements for carrying out the Vojta therapy and the evaluation of that scale. However, the assessment of the Infant Motor Profile (IMP) is performed by observing a protocolized video recording. This allows the quantification of this factor by an evaluator external to the service (in this case the external principal investigator). This will not only allow us to blind the evaluator regarding the type of intervention that the child receives, but also whether the video belongs to pre- or post-intervention groups. To do this, the videos will be sent after being encrypted and randomized for quantification. 

The study was approved by the Research Ethics Committee of the University of Murcia (1823/2018) and Comité de Ética de la Investigación de A Coruña-Ferrol (2022/099). This trial has been registered under the following code: ClinicalTrials.gov Identifier: NCT0609261.

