#### 2.3.2. Exclusion Criteria

The data of those patients who have had to apply another therapy (pharmacological, surgical, or rehabilitative) during the care provided by the physiotherapist in their usual clinical practice will not be included. For ethical reasons, this will not be explicitly explained to the families who agree to participate in this study, so as not to influence possible therapeutic decisions in the following two months. Data of the children will be followed up and can be excluded later if there is a change in their diagnosis and cerebral palsy is not confirmed at the appropriate age. The previous therapeutic trajectory, as well as concomitant treatment (such as pharmacological treatment for spasticity, dystonia, epilepsy, etc., as well as other rehabilitation interventions) was not considered within the exclusion criteria for two reasons: their effect would already be included within the rate of motor development before VT, and also because all the children were compared only to themselves. These will be noted and considered during the calculations, but the data exclusion will only occur if there are changes in them (both adding or withdrawal) during our 2 months of intervention. 

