### 2.6. Sample Size Calculation and Statistical Analysis

Sample size calculation: The prevalence of cerebral palsy is 2.08 cases/1000 births. To obtain a good sample security, 30 subjects for each of the groups to be evaluated offer a confidence interval of 95% with a security of 10.

The initial GMFM and IMP score will be divided by the child’s months of age to calculate the rate of acquisition of their items so far. This calculation represents the mean distribution of the acquisition of these motor items. The acceleration values will be used to avoid errors in the assumption of how these items were acquired, since the tendency is to be exponential at these ages. The net values obtained in the valuation will not be considered, but the rate with which they have been obtained as a function of time will be. The rate of this development without intervention will be calculated at the time of the initial assessment, relative to the age of the patient. The proportion of the score necessary to obtain in the next two months to be able to accelerate that rate, instead of following the same previous trajectory, will be an unknown concept for all therapists and examiners.

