## 3. Methods and Timeline

Phase 1. Initial Assessment: Children who go to the rehabilitation center where they have been referred will be treated, an initial routine clinical examination will be performed, including: Personal/medical data collection.GMFM quantification.Treatment with the physiotherapist.Training of the parents in the home program.Recording for the IMP quantification.

Phase 2. Intervention period (2 months): The assignment to the therapist will be randomized according to the needs of the service, where each therapist will adapt the treatment according to the initial assessment. Both assessors and therapist cannot be blinded to the allocation or treatment, and both required live-direct performance. An external assessor (blind to both) will be able to score the IMP recordings. 

Children will receive weekly or fortnightly treatment, and their parents, family members, or carer will be trained in carrying out a home program. Each therapist will adapt the treatment according to the initial evaluation, as is usually performed in the rehabilitation service. During the treatment sessions, the physiotherapist will apply the therapy directly, either based on Vojta therapy or conventional physiotherapy. The frequency of repetition of the treatment at home and in the hospital will be recorded, depending on the availability of each family and the normal functioning of the service.

Phase 3. Second assessment at 2 months (±1 week, depending on follow up appointments).

Collection of data on the possible changes made in previous treatments and the frequency of home treatment (possible incidents due to illness or family limitations).GMFM quantification.Recording necessary for IMP quantification.

Children carried on clinically with the intervention, but this short period would allow us to attribute changes to RL, controlling better the influence of other factor (such as age maturation or other therapy inputs).

Study length. The data collection will be carried out for 4 years from the approval of the CEI. Only patients receiving healthcare with any of the therapies under investigation after authorization by the CEI will be included.

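### The long-term goal has no assessment after 2 months, and the natural-history goal is only partly answerable because the baseline rate may include earlier therapy

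*Protocol article*

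**What the plan says.** Section 1.3 sets three secondary goals. Two matter here.

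- Goal 3 is a comparison between groups over the long term: "To assess the long-term impact on the gross motor function of children with neuromotor disorders undergoing Vojta therapy", set against children who do not receive it. No time horizon is attached.
- Goal 2 is "To study the natural history of the rate of development of gross motor function in children under one and a half years of age", continued as "with neuromotor alterations (pre-rehabilitation intervention".

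On timing, section 2.1 has gross motor function assessed before the intervention "and two months after its application". Section 3 ends with Phase 3: "Second assessment at 2 months (±1 week, depending on follow up appointments".

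On the baseline rate, section 2.6 divides the initial score by age and describes the result thus: "The rate of this development without intervention will be calculated at the time of the initial assessment". Section 2.3.2 then names "The previous therapeutic trajectory, as well as concomitant treatment" as something that does not exclude a child. One of its reasons is that any effect of such therapy is contained in the rate before Vojta therapy.

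**The concern.** An objective needs a measurement that can answer it. For goal 3 the schedule appears to supply none. If the goal stays as worded, it must either go unanswered or be answered with 2-month data that do not bear on it.

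For goal 2 the difficulty is what the baseline rate represents. A rate that includes the effect of earlier physiotherapy, surgery or botulinum toxin does not describe development before rehabilitation. If all children are pooled under the label in section 2.6, readers could take a mixture of treated and untreated development for natural history.

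**Working it through.** The plan gives no figure on this point to reproduce. The check sets the goals against the schedule, the eligibility rules and the definition of the rate.

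**Goal 3: is there any motor assessment after 2 months?**

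- Section 2.1: two assessments, before the intervention and at two months.
- Section 3, Phases 1 to 3: GMFM and IMP at the initial assessment and again at 2 months ± 1 week. No later phase is listed.
- Section 3, Statistical Methods: the time factor has two levels, pre-treatment and post-treatment.
- Section 3, after Phase 3: children continue in clinical care, with no further study measurement described. The short period is defended as helping attribution.
- Section 3, Study length: the 4 years is the duration of data collection for the whole study, not follow-up per child.
- Section 2.3.2: later follow-up is mentioned, but its purpose is to exclude children whose cerebral palsy is not confirmed. It includes no motor score.

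Scheduled motor assessments per child: 2. Assessments after 2 months: 0.

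**Goal 2: is the baseline rate an untreated rate?**

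- Section 1.3 asks for the rate before rehabilitation, under 18 months of age.
- Section 2.3 admits children from 0 to 36 months, so the sample may include children outside the goal's age limit.
- Section 2.6 calls the baseline score divided by age development without intervention.
- Section 2.3.2 admits children with previous or concomitant therapy and says its effect sits inside that rate.
- Section 4 says that relating the score to chronological age captures therapeutic as well as spontaneous experience since birth.
- Sections 2.5 and 4 list previous physiotherapy, occupational therapy, hydrotherapy, surgery and botulinum toxin as recorded data.
- No section restricts the natural-history analysis to untreated children.

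Even for an untreated child, section 4 builds the rate from one baseline score and an assumed score of zero at birth. It is therefore an average over the child's life so far, not an observed course.

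**How a bias would arise.** Suppose an untreated child gains s points per month, and earlier therapy raises this to s(1 + g) for the last T of A months of life.

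- Score at age A: s(A − T) + s(1 + g)T = s(A + gT).
- Score divided by age: s(1 + gT/A).
- Relative overstatement for that child: gT/A.

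The document gives no value for g or T, nor the share of children treated before. All values below are assumptions that show only how the formula behaves:

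| A (months) | T (months) | g | gT/A |
|---|---|---|---|
| any | 0 | any | 0% |
| 12 | 3 | 0.25 | 6.25% |
| 12 | 6 | 0.25 | 12.5% |
| 12 | 6 | 0.50 | 25% |
| 18 | 12 | 0.25 | 16.7% |
| 18 | 12 | 0.50 | 33.3% |

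These are shifts per treated child. If only a share q was treated and untreated rates are similar, the shift in the mean is q times as large. With q = 50% and the 6.25% row it is 0.5 × 6.25% = 3.1%.

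**The case against.** On goal 3 there is little to set against the point. The 4-year study length and the diagnostic follow-up are the only candidates for later data, and neither provides a motor assessment. A reader might infer that the 2-month result will be presented as long-term evidence. The article does not say so; it explains why the period is short, and the goal might simply go unreported.

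On goal 2 the defence is stronger. A reader might infer that the goal cannot be answered at all, or that sections 2.3.2 and 2.6 flatly contradict each other. The document does not support either reading.

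- Previous therapy is recorded, and section 2.3.2 says these treatments will be taken into account in the calculations. Section 4 adds that their influence on the results will be examined. How they enter the analysis may fairly be left to an analysis plan.
- The phrase in section 2.6 can mean without the study intervention, which is how section 4 uses pre-intervention. On that reading the sections agree and the label is merely loose.
- The wording of goal 2 can itself be read as limiting it to children not yet in rehabilitation.

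What survives is narrower: no methods section carries that limit through, and the label in section 2.6 invites the wrong reading.

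**Conclusion.** The point holds, with unequal force in its two parts.

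Goal 3 cannot be delivered by the design. This is a mismatch between a stated objective and a stated schedule, and an analysis plan cannot supply a visit that does not take place.

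Goal 2 is answerable in part, through a subset of previously untreated children under 18 months, and then only as an average rate per child. The plan as written does not commit to that subset.

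The size of any bias in goal 2 is unknown. It is zero if no child had earlier therapy, and the percentages in the working illustrate a mechanism and are not estimates. Both parts concern secondary goals. The main comparison of the two groups at 2 months is unaffected.

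**What to change.** - **Goal 3:** restate it as the 2-month impact compared with conventional physiotherapy, or delete it. Keeping the term long-term would need later scheduled GMFM and IMP assessments and a record of therapy received after 2 months, which is a much larger change.
- **Goal 2:** restrict the natural-history analysis to children under 18 months with no recorded prior rehabilitation, surgery or botulinum toxin, using the variables in sections 2.5 and 4. Report how many children that leaves. State that each rate is an average from one baseline score with an assumed zero at birth.
- **Section 2.6:** rename the baseline quantity *rate before study treatment*.

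The cost is wording plus one filter on data already being collected. Section 4 reports completed data on only four subjects so far, so the change is still easy to make. The downside is a narrower goal 3 and a natural-history subset smaller than the planned 60 children (30 + 30), by an amount the document does not allow one to predict.

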## 2. Materials and Methods

### 2.1. Study Design

A pseudo-randomized clinical trial has been designed that will assess gross motor function before the physiotherapy intervention (with Vojta therapy or conventional physiotherapy intervention, such as environmental enrichment and task-specific training) and two months after its application. The clinical trial has been conducted according to the consolidated standards of reporting trials (CONSORT) statement [40]. The current treatment protocol is described according to the recommendations of SPIRIT [41].

Patients are assigned to one treatment or another following criteria of immediacy as part of the regular routine of the rehabilitation service. Therefore, the randomization of the sample is possible following the natural ordering of the rehabilitation service where the study is carried out. The participants in this research, within their care routine and according to the health protocols established in the service, will be assigned to one of the two study groups:Intervention group: patients under Vojta Therapy intervention [17,18,19,20,21,22,23,24,25,26,27,28]Control group: patients under regular physiotherapy intervention, such as environmental enrichment and task-specific training [25]

This methodology will be useful to provide a service evaluation of the operation of the rehabilitation service itself.

Neither the therapists nor the evaluators of the GMFM may be blinded to the type of treatment administered due to the organization of the rehabilitation service where the study is carried out, as well as the “face-to-face” requirements for carrying out the Vojta therapy and the evaluation of that scale. However, the assessment of the Infant Motor Profile (IMP) is performed by observing a protocolized video recording. This allows the quantification of this factor by an evaluator external to the service (in this case the external principal investigator). This will not only allow us to blind the evaluator regarding the type of intervention that the child receives, but also whether the video belongs to pre- or post-intervention groups. To do this, the videos will be sent after being encrypted and randomized for quantification. 

The study was approved by the Research Ethics Committee of the University of Murcia (1823/2018) and Comité de Ética de la Investigación de A Coruña-Ferrol (2022/099). This trial has been registered under the following code: ClinicalTrials.gov Identifier: NCT0609261.

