### 2.4. Outcomes

Two of the most accepted scales in pediatric rehabilitation will be used, quantifying gross motor function from different aspects.

The first is the Gross Motor Function Measure (GMFM). Gross motor function and mobility have important roles for classification, assessment, and research involving children with neuromotor disorders [42,43,44]. The Gross Motor Function Measure [45] could be currently considered as gold standard for the quantification of gross motor function in the pediatric rehabilitation. These follow ups of thousands of children with cerebral palsy described the long-term development of their gross motor function and defined five unalterable levels of severity. By the age of six, stability over time on the prognosticated level of mobility is expected [45]. Even though the GMFM was not designed to assess outcomes of therapeutic interventions, some authors have used its centiles to compare individual effects. The use of the reference percentiles for the GMFM as outcome make it possible to estimate the change between two subsequent assessments and to directly compare gross motor improvement across ages and Gross Motor Function Classification System (GMFCS) levels. On the other hand, uncompleted items of GMFM assessments are used as short-term therapeutic goals and, therefore, individually controlled comparison of the rate of acquisition of gross motor function seems to be possible within each range. 

The Infant Motor Profile (IMP) scale [46] is another evidence-based method of assessing infant motor behavior. It not only quantifies motor milestones, but also tests movement quality by analyzing five factors: variability, adaptation, symmetry, fluency, and capacity. The advantage of this scale is that the assessment is performed through video recording, allowing us to have a dedicated clinical evaluator blinded to the type of intervention. 

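### Encryption and random order cannot assure that the IMP rater is blind to time point, so only the between-arm difference in IMP change should be claimed as blinded

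*Protocol article*

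**What the plan says.** Section 2.1 (Study Design) of the protocol article states that the therapists and the GMFM evaluators cannot be blinded. The IMP is offered as the exception because it is scored from a standardised video "by an evaluator external to the service (in this case the external principal investigator". Two masks are then claimed for this rater: the type of intervention, "but also whether the video belongs to pre- or post-intervention groups". The means are that "the videos will be sent after being encrypted and randomized for quantification". The article describes no other masking step.

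The mask is described more narrowly elsewhere. Section 2.4 (Outcomes) gives the advantage of video as "allowing us to have a dedicated clinical evaluator blinded to the type of intervention" and does not mention time point. Section 3 (Methods and Timeline) says "An external assessor (blind to both) will be able to score the IMP recordings", directly after a sentence about allocation and treatment.

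Three other parts of the article bear on the point. Section 2.3.1 admits children from 0 to 36 months. Section 3 sets the second assessment at 2 months, plus or minus 1 week. Section 2.3.2 justifies the handling of earlier and concomitant treatment partly on the ground that "all the children were compared only to themselves".

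**The concern.** Encrypting and shuffling files removes the file name, the date and the order of recording. It leaves the child's size and motor stage in view. The IMP scores motor milestones and movement quality, so what is being rated is also a clue to which recording came later. If one person scores both recordings of a child and recognises the child, the time point can be inferred.

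This matters because the article leans on before/after inference as well as on the comparison of arms. Section 2.3.2 treats each child as its own control, and Section 3 argues that the short interval lets changes be attributed to the therapy. The IMP is the only scale with any masking. A rater who expects improvement and can tell the order might score the later video higher. The resulting within-child gain would then be reported as blinded evidence. The named rater is the external principal investigator of a study whose main goal (Section 1.2) is to demonstrate change, so expectation is a realistic source of bias.

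**Working it through.** The article gives no figure for the quality of the masking, so there is nothing to reproduce. The check has three parts.

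**1. How visible is two months?** Inputs: the 2-month interval (Section 3) and the age range 0 to 36 months (Section 2.3.1). Interval as a share of age at the first video:

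| Age at first video (months) | 2 / age |
|---|---|
| 2 | 100% |
| 3 | 67% |
| 6 | 33% |
| 12 | 17% |
| 24 | 8% |
| 30 | 7% |
| 34 | 6% |

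This is only a rough guide to visible change. It suggests that order is likely to show in young infants and much less surely at 2 to 3 years. Section 2.6 says of item acquisition "since the tendency is to be exponential at these ages". That describes the shape of the curve and fits fast change, but it does not show that two months is obvious on a video.

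**2. What could a leaning do to a within-child test?** Inputs: 30 children per arm (Section 2.6) and the 5% level (Statistical Methods), taken as two-sided because the sidedness is not stated. Assumption: with no true change, the rater adds b standard deviations (SD) of the change score to every later video. The documents give no value for b, so a range is shown.

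The mean leaning that would by itself sit at the significance threshold with n = 30 is t(0.975, 29)/√30 = 2.045/5.477 = 0.373 SD.

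The rejection rate comes from the noncentral t with noncentrality b√n. The one-arm test has 29 degrees of freedom. The time effect over both arms (n = 60) has 58.

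| b (assumed) | b√30 | One arm, n = 30 | b√60 | Both arms, n = 60 |
|---|---|---|---|---|
| 0 | 0 | 5% | 0 | 5% |
| 0.1 | 0.55 | 8% | 0.77 | 12% |
| 0.2 | 1.10 | 19% | 1.55 | 33% |
| 0.3 | 1.64 | 36% | 2.32 | 63% |

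A normal approximation, 1 − Φ(1.96 − b√n) + Φ(−1.96 − b√n), gives similar values: 19.5% and 37.6% for b = 0.2 and 0.3 with n = 30, and 34.1% and 64.2% with n = 60.

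**3. What does it do to the between-arm contrast?** If the leaning is b in both arms, the expected difference in change is (δV + b) − (δC + b) = δV − δC, where δV and δC are the true changes under Vojta and conventional therapy. The bias is zero and the test stays at 5%. A rater who does not know the arm has no route to lean by arm, so the group-by-time term of the repeated-measures ANOVA is protected as long as the arm mask holds.

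**The case against.** The strongest reply is that the time mask may work better than this suggests. The evaluator is outside the service, the files are coded, and complete data would give 60 × 2 = 120 videos in random order. A single video of an unknown child of unknown age does not show whether it is the first or the second. The rater must first match it to its pair, and nothing in the article says that the rater can do so. This stands in part. A reader might infer that the time point cannot be hidden at all, or that the IMP change is not blinded in any sense. The documents support neither reading. Masking is doubtful in the youngest infants and may hold for many children of 2 to 3 years, and the mask on treatment arm is not in question. That one person scores both videos is implied by the single named evaluator but not stated.

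A second reply concerns the false-positive figures. Zero change is not an interesting null in children who mature over two months anyway, and Section 2.6 works with rates rather than net scores. The planned analysis is a two-group ANOVA with Bonferroni correction, not an uncorrected one-arm test. This also stands. The figures show how sensitive a within-child test is to a modest leaning; they do not estimate the error rate of the planned comparison.

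Third, it is tempting to say that order of arrival gives the time point away. The article does not say that baseline videos go out as they are recorded, and randomising before sending suggests pooling. A release schedule is also detail that an article may leave to the full protocol. The release rule below is therefore a precaution, not the correction of a stated error.

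Finally, the rate and acceleration comparisons set out in Section 4 concern the GMFM, which is openly unblinded. They do not depend on the IMP mask and are no evidence for this point.

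**Conclusion.** The point holds in a limited form. Section 2.1 states as a fact that the rater will not know whether a video is pre or post, and the means it gives cannot assure this, at least in the youngest infants. What is exposed is the within-child pre/post IMP change, in either arm or pooled. The between-arm difference in IMP change is not exposed, provided that the arm mask holds and any leaning toward the later video is equal in the two arms.

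The size of any bias is unknown. The 19% and 36% rejection rates rest on assumed leanings of 0.2 and 0.3 SD, on no true change and on a one-arm test with 30 children. The conclusion also assumes that the one named evaluator scores both recordings of a child. The correction is worth making because the article relies on within-child change and attributes it to therapy, and because the cost is very small.

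**What to change.** - **Wording in Section 2.1.** Limit the assured blinding claim to treatment arm. Describe encryption and random order as reducing, not removing, knowledge of the time point. This also brings Section 2.1 into line with Section 2.4.
- **Blinded conclusion.** State that the blinded IMP result is the between-arm difference in change, that is, the group-by-time term of the ANOVA in Statistical Methods. Report within-arm IMP change as not assuredly blind to time.
- **Release of videos.** Send videos for scoring only once both recordings of a child exist, in random order across children, with a child's two videos kept apart in the scoring sequence. This limits cues from sequence and direct comparison but does not remove cues from growth, so the wording change is still needed.

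The cost is a few sentences and a release rule, with no extra rater or visit. Scoring starts about two months later, and the within-arm IMP claim becomes weaker. The change is still timely, since Section 4 reports complete assessment data on only four children.
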